## Abstract

**Background:**

Several intervention studies have demonstrated that exercise training has beneficial effects among cancer patients. However, older cancer patients are underrepresented in clinical trials, and only few exercise-based studies have focused specifically on older patients with cancer. In particular, research investigating the effects of exercise training among older patients with advanced cancer is lacking. The purpose of the current study is to investigate the effect of a 12-week multimodal and exercise-based intervention among older patients (≥65 years) with advanced pancreatic, biliary tract or lung cancer, who are treated with first-line palliative chemotherapy, immunotherapy or targeted therapy.

**Methods:**

PACE-Mobil-PBL is a two-armed randomized controlled trial. Participants will be randomized 1:1 to an intervention group (*N* = 50) or a control group (*N* = 50). Participants in the intervention group will receive standard oncological treatment and a 12-week multimodal intervention, comprised of: (I) supervised exercise training, twice weekly in the hospital setting, (II) home-based walking with step counts and goal-setting, (III) supportive and motivational nurse-led counseling, and (IV) protein supplement after each supervised training session. Participants in the control group will receive standard oncological treatment. The primary outcome is physical function measured by the 30-s chair stand test. Secondary outcomes include measures of feasibility, activity level, physical capacity and strength, symptom burden, quality of life, toxicity to treatment, dose reductions, inflammatory biomarkers, body weight and composition, hospitalizations and survival. Assessments will be conducted at baseline, and after 6, 12 and 16 weeks.

**Discussion:**

The current study is one of the first to investigate the effect of an exercise-based intervention specifically targeting older patients with advanced cancer. PACE-Mobil-PBL supports the development of health promoting guidelines for older patients with cancer, and the study results will provide new and valuable knowledge in this understudied field.

**Trial registration:**

The study was prospectively registered at ClinicalTrials.gov on January 26, 2018 (ID: NCT03411200).

**Electronic supplementary material:**

The online version of this article (10.1186/s12885-018-4835-2) contains supplementary material, which is available to authorized users.

## Background

Advanced age is the leading risk factor for development of cancer overall, and approximately 60% of all cancers in Europe and in the USA are diagnosed among patients aged 65 years or older [1, 2]. Although the risk of cancer increases with age, and the number of older patients with cancer is expected to rise in the coming years [3, 4], research on older patients with cancer is limited [1, 4]. Aging involves a continuum of changes in function, biological, psychological, and social structures that vary depending on individual differences. In a biological view, aging causes changes in the organism that lead to a decline in organ functions and in physiological reserves [5–8]. Comorbidity, defined as the occurrence of two or more medically diagnosed diseases, increases with age and heightens the risk of disability and mortality [9, 10]. In addition, use of multiple drugs for multiple diseases, also known as polypharmacy, leads to an increased risk of drug interactions, adverse reactions and poor adherence [11].

### Cancer and aging

Aging itself is associated with limitations in physical function and reduced reserve capacity. A diagnosis of cancer and its accompanying treatments can lead to numerous symptoms and side effects, physical disability, psychological distress and increased health care needs [12]. The interplay between age-related and cancer-related declines in health increases vulnerability and risk of development of short- and long-term disabilities [13, 14]. Older patients with cancer have a higher incidence of limitations in activities of daily living (ADL), reduced quality of life (QoL), and a higher prevalence of geriatric syndromes such as depression, falls and osteoporosis compared to older adults without a history of cancer [15, 16]. Research suggests that older patients with cancer benefit from chemotherapy similar to younger patients [17, 18]. However, older patients with cancer are at increased risk of toxicity due to age-related physiological changes [19].

### Sarcopenia and cachexia

Loss of muscle mass and strength is a part of the normal aging process and is referred to as primary sarcopenia [20]. Sarcopenia has multiple contributing factors including aging itself, insufficient nutrition, sedentary lifestyle or bedrest. The term secondary sarcopenia is often used to describe sarcopenia that is caused by other factors such as cancer or other chronic diseases [20]. Cachexia is another depleting syndrome that causes weight loss and muscle wasting due to an underlying disease [21]. The pathophysiology of cancer cachexia includes a complex combination of reduced energy intake and uptake, hormonal alterations, abnormal metabolism and inflammation [21]. Previous studies have identified cachexia and sarcopenia as contributors to impaired physical functioning [22], reduced tolerance to anti-cancer treatment [23, 24], higher symptom burden [25], reduced QoL [25, 26] and increased mortality [24, 27, 28] among patients with cancer.

### Exercise training

Research has shown that exercise training (e.g. aerobic training, resistance training, and balance and flexibility exercises) is safe and beneficial for older people [29–31]. Documented effects include increased muscle mass and strength, functional mobility and ADL function, improved QoL, and reduction of falls and depressive symptoms [29–32]. The effect of exercise training has also been widely investigated in cancer patients [33–35]. A myriad of beneficial effects of exercise training have been documented, including reduced severity of cancer and treatment-related symptoms and side effects, as well as improved aerobic capacity, muscle strength, physical functioning and QoL [33–36]. However, older patients are underrepresented in clinical trials, and only few exercise-based intervention studies have focused specifically on older patients with cancer [37]. Among the few studies that have investigated the effect of exercise training in older patients with cancer, most have focused on older patients with early-stage breast, prostate and colorectal cancer. Especially, research investigating the effect of exercise training in older patients with advanced cancer is lacking [37].

### Pancreatic, biliary tract and lung cancer

With median ages around 65 to 70 years at diagnosis, pancreatic cancer (PC), biliary tract cancer (BTC) and lung cancer (LC) are malignancies highly associated with aging. These cancers are most often diagnosed at an advanced stage, and therefore the majority of patients are treated with palliative therapies. Focusing on LC, several previous studies have provided evidence that exercise training is feasible, safe and beneficial for patients with LC before, during and after anti-cancer treatment [38–41]. Demonstrated effects include reduced surgical complications, reduced levels of symptoms and side effects, and improvements in physical function and capacity [38–41]. Only one prior exercise-based study has focused specifically on older patients with LC. In this study, Lai et al. [42] investigated the effect of a short-term preoperative pulmonary rehabilitation program in 60 older patients (≥70 years) with non-small cell LC (NSCLC) scheduled to lobectomy, and demonstrated significant improvements in functional capacity and peak expiratory flow, as well as reductions in length of hospital stay and post-operative complications. Exercise training for patients with PC and BTC is a relatively unexplored research field. In a randomized controlled trial, Yeo et al. [43] investigated the effect of a 12-week home-based walking program in 102 patients with resected PC or periampullary cancer. After study completion, patients in the intervention group were walking twice as far as patients in the control group, and had significant reductions in pain and fatigue, as well as improved self-reported physical functioning [43]. In a pilot study from 2014, Jensen et al. [44] investigated the feasibility of exercise training in 26 patients with advanced gastrointestinal cancers undergoing palliative chemotherapy. Patients were randomized to one of two groups; resistance training or aerobic exercise on a bicycle ergometer for 12 weeks. In both groups, a significantly decreased level of fatigue was demonstrated from pre to post-assessment, and sleep quality was also significantly improved. However, only minor improvements were seen in a few domains of QoL measures, and no improvements were demonstrated in nausea/vomiting, constipation, dyspnea or appetite/anorexia [44]. No prior studies have investigated the effect of an exercise program specifically for older patients with PC or BTC.

### Aim

The aim of the current study is to investigate the effect of a 12-week multimodal and exercise-based intervention in older patients newly diagnosed with advanced PC, BTC or LC who are undergoing first-line palliative chemotherapy, immunotherapy or targeted therapy.

### Hypothesis

We hypothesize that with a multimodal and exercise-based intervention, participants will maintain physical function. In addition, we believe that participants in the intervention group will have reductions in symptoms and side effects, improved QoL and psychological wellbeing, limited weight loss and muscle wasting, and increased treatment tolerance, compared to participants in the control group.

## Methods

### Design

PACE-Mobil-PBL is a prospective two-armed randomized controlled trial. The study is planned to include 100 patients with advanced PC, BTC or LC, who are treated with first-line palliative chemotherapy, immunotherapy or targeted therapy at the Department of Oncology at Copenhagen University Hospital, Herlev and Gentofte, Denmark. The overall study design is illustrated in Fig. 1. This article describes the design of the study and complies with the SPIRIT guidelines for randomized controlled trial protocols, and with the Consensus on Exercise Reporting Template (CERT) recommendations for reporting exercise programs in clinical trials [45].

**Fig. 1 Fig1:**
[figure not shown]
PACE-Mobil-PBL study design. Abbreviations: BTC (biliary tract cancer), LC (lung cancer), PC (pancreatic cancer)

### Participants

Patients are eligible for inclusion if the following criteria are fulfilled: 1) diagnosis with locally advanced or metastatic PC, BTC or NSCLC within 12 weeks; 2) unresectable cancer; 3) treatment with first-line palliative chemotherapy, immunotherapy or targeted therapy; 4) age ≥ 65 years; 5) Eastern Cooperative Oncology Group (ECOG) performance status score ≤ 2; 6) ability to speak and read Danish, and to provide a signed informed consent form (ICF).

Exclusion criteria are: 1) any physical condition that hinders the execution of physical exercise training; 2) small-cell LC; 3) documented and uncontrolled brain metastases that hinder study participation based on the referring oncologist’s assessment; 4) dementia, psychotic disorders or cognitive diseases or conditions that hinder participation in an exercise-based clinical trial; 5) unstable medical disease or a history of serious or concurrent illness (any medical condition that might be aggravated by exercise training or that cannot be controlled). Patients with documented bone metastases will be excluded from participation if they have a bone metastatic burden or location that poses a risk of pathologic fractures in the performance of exercise training, as assessed by the referring oncologist.

After the initial screening procedure, the research team will obtain ICF and collect all relevant baseline data before randomization.

### Patient involvement

With the aim of involving patients in the research process, individual semi-structured interviews were conducted in older patients with advanced PC, BTC and LC, before the final intervention program was developed. The aim of these pre-interviews was to gain insight into how patients experience and manage symptoms and side effects, to explore their views on exercise training during oncological treatment, and to get their expert advice on the optimal recruitment procedure, intervention composition, and on relevant outcome measures (unpublished results).

### Randomization

After inclusion and baseline assessments, participants are randomly allocated to the intervention group or the control group using a 1:1 block randomization. The block size will only be known by the statistician carrying out the randomization procedure. Randomization will be stratified on diagnosis by using separate randomization lists for each diagnosis group (PC, BTC and LC). The ‘blockrand’ package of the statistical software R was used to generate all randomization lists. Randomization will be administered via the web-based research platform REDCap (Research Electronic Data Capture). Source codes to generate all randomization lists are stored to ensure full reproducibility.

### Intervention

Participants in the intervention group will receive standard oncological treatment and a 12-week multimodal exercise-based intervention comprised of the four following components:*Supervised and group-based exercise training at the hospital setting;* two times a week for sessions of approximately 60 min. The program consists of warm-up exercises of light to moderate intensity, including exercises for balance and flexibility, and a program of progressive resistance training (PRT) that comprises seven resistance training exercises targeting the large muscle groups. In the first two weeks, participants will be introduced to the PRT program, starting with high repetition numbers and low loads. During the intervention period, the volume of the PRT will progress from two to three sets, and the load will increase from 15 to 10 repetitions maximum (yielding a heavier load relative to each participant’s maximum). The progression will be tailored to each individual participant. Three experienced physiotherapists (range 6–17 years) will supervise all training sessions. Training sessions will be performed in groups of up to 12 participants at the rehabilitation facilities at Herlev and Gentofte Hospital, where appropriate strength training equipment is available (Technogym Element series, Gambettola, Italy). For detailed description of the supervised exercise program see Table 1.*Nutritional supplement after supervised exercise training*; to prevent a negative energy balance on training days, a protein supplement (e.g. protein drink or bar, 227–300 cal and 12–20 g protein) will be served for participants after each training session.*An individualized activity program with steps counts, goal-setting and evaluation;* based on each participant’s starting point, preferences and motivation, an individualized activity program will be conducted with the overall aim of maintaining or increasing the level of daily activity. The level of activity will be measured as steps counts with a Garmin Vivofit 3 activity tracker (Garmin, Olathe, Kansas, U.S.). Goal-setting and evaluation in relation to walked steps will be conducted once weekly, face-to-face or by telephone, in collaboration between each participant and a member of the research team.*Motivational and supportive counseling;* participants in the intervention group will participate in two sessions of individualized nurse-led counseling. The first session will be held immediately after study entry, and the second will be conducted after 6 weeks. Counseling will be based on a holistic assessment of each participant’s life situation and potential challenges. Each participant will be asked about potential problems in different life domains (physical, functional, psychological/emotional, social, and existential/spiritual). Based on identified needs, participants will be challenged with questions about the characteristics of the problem(s), factors that may influence the problem(s), and their problem management strategy. The purpose of this process is to activate the participants and to promote self-management. Also, advice and counseling on identified problems will be provided, and followed up if needed. If participants present any complex medical problems, they will be encouraged to contact their oncologist or general practitioner, as appropriate. As mandatory components, all participants will be informed about expected bodily reactions to exercise training, and advised about sufficient nutrition during the intervention. If participants need specialized nutritional counseling, they will be referred to a dietician.

**Table 1 Tab1:** Description of the supervised exercise program

Duration of exercise program	12 weeks (24 sessions)
Duration of exercise sessions	60 min (10 min of warm-up, 45 min of PRT and 5 min of stretching)
Exercise frequency	2 times a week
Rest period between exercise sessions	2–5 days
Warm-up	Exercises of light to moderate intensity with elements of balance and flexibility training (e.g. walking around in circles with changing directions, walking on toes and heels, floor touch, walking lunges, exercises on balance board)
Description of PRT exercises	Chest press, abdominal crunch, leg press, leg curl (hamstrings), leg extension (quadriceps), lower back and low row
No. of repetitions (PRT)	15 RM (session 1–2), 12 RM (session 3–13), 10 RM (session 14–24)
No. of sets per session (PRT)	2 (session 1–6), 3 (session 7–24)
Rest period between sets (PRT)	60 s

Abbreviations: No. (number), *PRT* progressive resistance training, *RM* repetition maximum

### Controls

Participants in the control group will receive standard oncological treatment. No restrictions on physical activity are made for control participants.

### Study outcome measures

The primary endpoint is the between-group difference in within-group changes in physical capacity and lower extremity strength measured with the 30-s chair stand test (30s-CST) at the post-intervention assessment. Secondary endpoints include feasibility measures, adverse events, and changes in functional performance, muscle strength, body composition, body weight, patient-reported performance status, symptom burden, symptoms of depression and anxiety, QoL, physical activity, treatment tolerance and toxicity, inflammatory biomarkers, hospital admissions and mortality. The outcome measures for both groups are described in the following section.

#### Physical tests

To measure physical function and lower extremity strength, the 30s-CST will be used (primary outcome) [46]. The 30s-CST is considered as highly relevant for older patients with cancer, as the ability to rise from a chair is regarded a prerequisite for functional independence. The 30s-CST is a widely used and validated physical measure, especially among older people, and it has also been used and tested among patients with cancer [47–49]. Physical performance will also be assessed with a 6 and 10-m gait speed test. Gait speed is a suitable measure to use in a clinical rehabilitation setting, and has a documented predictive value for functional and cognitive decline, falls, independence, and mortality [50, 51]. To measure physical capacity and endurance, the six-minute-walk test (6MWT) will be used [46]. The 6MWT measures the distance an individual is able to walk over a total of six minutes on a hard and flat surface. The test was originally developed for use in frail older patients, but has been used and validated in a variety of different populations [52, 53]. To measure physical function and strength of the upper body, the handgrip strength test will be used [54]. Research has shown that handgrip strength may be independently associated with functional capacity, QoL and survival in patients with advanced cancer [55]. Detailed descriptions of the performance of physical tests can be found in an additional file (see Additional file 1).

#### Feasibility measures

Feasibility of the intervention will be evaluated as acceptability, attrition and adherence. Acceptability will be measured as the number of eligible patients who agree to participate in the study. Reasons for declining study participation will be listed and evaluated. Attrition will be registered as the number and percentage of participants who do not complete the study requirements. For each component of the intervention adherence will be assessed as the percentage of study parts completed. Data on adverse events related to the intervention will be monitored according to the National Cancer Institute Common Terminology Criteria for Adverse Events, version 4.0 (NCI CTCAE v4.0).

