#### Treatment tolerance and toxicity

Data on dose-reductions and treatment discontinuations will be registered prospectively throughout the intervention period. Toxicity will be registered according to the NCI CTCAE v4.0.

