#### Mortality/survival

Incidences of deaths and causes of deaths will be registered throughout the study period by review of medical records.

Frequency and timing of study assessments are shown in Table 2. REDCap will continuously be used for data entry during the study period, and subsequently for data storage.

**Table 2 Tab2:** Schedule of study assessments

Time (week no.)	-2 to 0	0	1	2	3	4	5	6	7	8	9	10	11	12	13	17
Enrollment																
Eligibility screen	X															
Informed consent	X															
Randomization		X														
Intervention			X---------------------------------------------------------------------------------------------------------------------------X													
Physical tests and examinations																
30s-CST (primary outcome)	X								X						X	X
6MWT	X								X						X	X
Handgrip strength	X								X						X	X
Gait speed test	X								X						X	X
Physical activity^a^	X														X	
DXA	X														X	
BI	X														X	
Body weight^a^	X								X						X	X
Inflammatory biomarkers	X								X						X	X
PROMs																
PRPS	X								X						X	X
MDASI^a^	X								X						X	X
EORTC-QLQ-C30	X								X						X	X
HADS	X								X						X	X
Qualitative exploration																
Individual Interviews															X	
Feasibility																
Adherence	X	X	X	X	X	X	X	X	X	X	X	X	X	X		
Attrition	X	X	X	X	X	X	X	X	X	X	X	X	X	X	X	X
Adverse events	X	X	X	X	X	X	X	X	X	X	X	X	X	X		
Oncological treatment																
Treatment related toxicity^b^	X	X	X	X	X	X	X	X	X	X	X	X	X	X	X	X
Dose-reductions^b^	X	X	X	X	X	X	X	X	X	X	X	X	X	X	X	X
Hospitalizations	X	X	X	X	X	X	X	X	X	X	X	X	X	X	X	X
Survival	X	X	X	X	X	X	X	X	X	X	X	X	X	X	X	X

^a^Once weekly for participants in the intervention group ^b^Registered for every treatment course

Abbreviations: *30s-CST* 30-s chair stand test, *6MWT* six-minute-walk-test, *BI* bioelectrical impedance, *DXA* whole-body dual-energy x-ray absorptiometry, *EORTC-QLQ-C30* European Organisation for Research and Treatment of Cancer Quality of Life Questionnaire C30, *HADS* Hospital Anxiety and Depression Scale, *MDASI* M.D. Anderson Symptom Inventory, *PRPS* patient-reported performance status

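### As described, the adverse-event endpoint covers intervention-related events to week 12, so it cannot compare the arms on falls, non-admitted fractures or musculoskeletal injuries

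*Protocol article*

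**What the plan says.** Study outcome measures names adverse events separately from feasibility: "Secondary endpoints include feasibility measures, adverse events, and changes in functional performance". It closes by telling the reader that "The outcome measures for both groups are described in the following section".

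The only later description of adverse-event collection is under Feasibility measures: "Data on adverse events related to the intervention will be monitored", graded by NCI CTCAE v4.0. The Controls section says "Participants in the control group will receive standard oncological treatment", with no restriction on their own physical activity.

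In Table 2 the row "Adverse events" is marked from the pre-randomization column through week 12 and is blank at weeks 13 and 17.

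Three other sources of safety data are described:
- Treatment tolerance and toxicity: "Toxicity will be registered according to the NCI CTCAE v4.0". In Table 2 the toxicity row stands under oncological treatment with the footnote "Registered for every treatment course".
- Hospital admissions: counts, causes and lengths of stay, from medical records.
- Mortality/survival: deaths and their causes, from medical records.

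Table 2 marks all three through week 17.

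**The concern.** An endpoint announced for both groups is defined so that one group cannot contribute to it. A count of intervention-related events is a reasonable description of how the programme was tolerated. It cannot show whether training raises or lowers the frequency of events that older patients with advanced cancer have anyway.

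The protocol gives reasons to want that answer. Its Background reports more falls and osteoporosis in older patients with cancer than in older adults without such a history, and cites fewer falls as a documented effect of exercise in older people. The Abstract says that the trial supports guideline development. A fall at home that is put down to age or disease would not enter the endpoint in the intervention arm, and no fall in a control could enter it at all.

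The schedule adds two mismatches. Collection stops before the physical tests of weeks 13 and 17, and it is marked before there is an intervention to which an event could be related.

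**Working it through.** No figure in the plan bears on this point; the sample-size calculation concerns the chair stand test alone. The check sets the sections side by side and counts the marks in Table 2.

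**1. Who can have a qualifying event.** Study outcome measures: both groups. Feasibility measures: events related to the intervention. Controls: standard oncological treatment, no intervention. The control count is therefore zero by definition, whatever happens to the patients.

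**2. When events are captured.** Table 2 has 16 time columns: -2 to 0, 0, weeks 1 to 12, 13 and 17 (1 + 1 + 12 + 2 = 16).

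| Row | Columns marked | Last mark |
|---|---|---|
| Adverse events | 14 of 16 | week 12 |
| Treatment-related toxicity | 16 of 16 | week 17 |
| Hospitalizations | 16 of 16 | week 17 |
| Survival | 16 of 16 | week 17 |

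The chair stand, six-minute walk, handgrip and gait tests are marked at baseline and in weeks 7, 13 and 17, which correspond to the assessments after 6, 12 and 16 weeks. The last two of these fall after the final adverse-event mark. Two of the 14 adverse-event marks (-2 to 0, and 0) precede the start of the intervention in week 1.

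**3. What the other data cover.**

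| Event | Recorded in controls? |
|---|---|
| Toxicity of the oncological treatment | Yes, by treatment course |
| Any event leading to admission | Yes, with cause |
| Death | Yes, with cause |
| Fall, non-admitted fracture or musculoskeletal injury not attributed to oncological treatment | No described place |

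The last row is the gap. In the intervention arm such an event is counted only if it is judged related to the intervention.

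**4. Direction of the error in that row.** Let each arm have 50 participants and true risk *p* of such an event. The expected true number is 50*p* per arm. The endpoint reports 0 for controls and between 0 and 50*p* for the intervention arm, depending on attribution. With an assumed *p* of 10%, 50 × 0.10 = 5: controls report 0 and the intervention arm 0 to 5, although the true difference is nil. The 10% is not from the protocol and the argument does not need it. For any *p*, the reported difference (intervention minus control) is zero or positive, so a reduction in falls could never appear. The intervention-arm count taken alone can only be correct or too low.

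**The case against.** A reader might infer that the trial's whole safety assessment rests on attribution by unblinded staff and that serious events in controls go unseen. The document does not support this. Admissions and deaths are collected with causes and without regard to relatedness, toxicity is not filtered by relatedness to the intervention, and all three run through week 17. A fracture or cardiac event that led to admission or death would be recorded in either arm. Nor does the article say who assesses relatedness. That the assessor knows the arm is a reasonable inference, since relatedness to an exercise programme is hard to assess without knowing who exercised, but it remains an inference.

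It can also be said that the sentence about both groups introduces a section containing items that cannot apply to controls, such as adherence to intervention components and interviews with intervention participants. On that reading adverse events are a descriptive feasibility measure, no between-arm test of them is promised, and a stop at week 12 matches a 12-week programme. The article also does not state that unrelated events are discarded, and the pre-intervention marks in Table 2 may hint at wider capture. Finally, eligibility excludes patients whose bone metastases carry a fracture risk during training, so the stakes should not be exaggerated.

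Most of this stands, and it limits the point. It does not remove it. Adverse events are named as an endpoint alongside feasibility, not only within it. No collection other than that of related events is described. If the Table 2 marks mean something wider, the table and the text disagree. Toxicity also carries an attribution label of its own, to the oncological treatment, so an injury attributed to neither drug nor exercise has no described place in either arm. And this is not a detail to leave to an analysis plan, because no analysis can restore events that were not recorded.

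**Conclusion.** The point holds in limited form. The adverse-event endpoint, as described, has no possible control-arm events, supports no between-arm comparison, ends before two rounds of physical tests, and is scheduled before the exposure that defines it. The loss is confined to events that are neither treatment toxicity nor a cause of admission or death, chiefly falls, non-admitted fractures and musculoskeletal injuries. How many would be missed cannot be derived from the protocol.

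The conclusion assumes that the Feasibility measures sentence describes the whole of adverse-event collection, as nothing else in the article suggests otherwise. It does not depend on any assumed event rate or on who judges relatedness. The primary endpoint and the other safety measures are untouched. Label: cheap improvement.

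**What to change.** Reconcile Study outcome measures, Feasibility measures and Table 2:

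- Record falls, fractures, musculoskeletal injuries and all serious events in both arms, regardless of attribution.
- Elicit them with the same questions at the existing baseline, 6-, 12- and 16-week assessments, and extend the adverse-event row of Table 2 through week 17. An injury during a physical test should be noted at that test, since no later visit follows week 17.
- Report by randomised group, and keep relatedness to the intervention as a descriptor of each event.

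The cost is a few REDCap fields at visits that already take place in both arms. There is one real downside. The intervention arm has two supervised sessions and one goal-setting contact per week with no counterpart in controls, so its events are more likely to be noticed. The between-arm comparison should therefore rest on events elicited at the common assessments; events noted at training sessions can be listed separately for the intervention arm.
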